#### 3.4.1 Blinding

It will be clear to most patients whether or not they have been assigned to the intervention or usual care arm of the study. Thus, it is not possible to blind patients to their group allocation. However, the randomisation procedure outlined above ensures that those involved in data collection and analysis will not know to which group patients have been randomly assigned.

### 3.5 Intervention

The complex intervention is referral to a VR service in either Tayside or Lothian (Figure 1). Patients recruited from PRI and Ninewells, Dundee are randomised to receive referral to a VR service in Tayside; individuals enrolled from WGH are referred to a VR service in Lothian. All participants allocated to the intervention arm of the trial are contacted by a VR service by telephone within 10 days following return of the baseline questionnaire to the researcher (RGK). Participants are allocated a 'case manager' who conducts a telephone assessment of supportive care needs to facilitate remaining in or returning to work during which baseline measures are also recorded using the Canadian Occupational Performance Measure (COPM) [13], 12 item General Health Questionnaire (GHQ-12) [14] and European Quality of Life - 5 Dimensions (EQ-5D) [15]. Outcomes are re-measured at 3- and 6-months from referral. Based on this initial assessment of each individual's personal goals and health status the case manager signposts participants to appropriate support services including physiotherapy, occupational therapy, occupational health nurse, occupational health doctor, counsellor/psychological therapy, complementary therapy. Each individual may therefore receive a different (combination of) intervention(s). Usual care following surgery involves no formal employment support. Participants in both arms of the trial receive a copy of the booklet *Work and Cancer *published by Macmillan Cancer Support [16].

As the personalised and complex nature of the intervention precludes exogenous standardisation, data will be obtained from each service on the specific interventions received by individuals in the intervention arm of the pilot RCT. Secondary analysis of outcome measures recorded by each service at initial assessment and 3- and 6-month follow up will also be undertaken for these women. In addition, information will be gathered about each service (e.g., size, workforce composition, ethos) to contextualise possible differences in reported outcomes between VR services.

### 3.6 Data collection

Data to evaluate the intervention in terms of quality of life, fatigue and change in employment status are collected at baseline, 6 months and 12 months after entry to the trial via a self-completion questionnaire. In addition, self-reported sickness absence is collected every four weeks for the first 6 months of follow-up and for the four weeks before the 12-month follow-up time point (Figure 1). A telephone reminder is administered if questionnaires are not returned within 10 days. Participants have the option of a researcher collecting their responses to all questionnaires by telephone.

### 3.7 Outcome measures

#### 3.7.1 Primary outcome

The primary outcome measure is self-reported number of days off work due to ill-health within the first six months after surgery.

There are two main ways of measuring absence from work: (1) sick leave register at participants' place of employment; (2) participant self-report. Although a sick leave register managed by the employer is regarded as the gold standard, self-report is also robust [17]. One study found more than 96% accuracy between register and self-report when the recall period is limited to 2 to 4 weeks [18]. The feasibility of using sick leave registers will be determined by asking participants to consent to contact with their employers to access their sick leave register at the end of the 6 month follow-up period.

#### 3.7.2 Secondary outcomes

Secondary outcome measures are changes in quality of life (QoL), fatigue and employment status.

##### 3.7.2.1 Quality of life

The Functional Assessment of Cancer Therapy-Breast Cancer (FACT-B) Version 4 will be used to assess breast cancer related QoL [19]. The FACT-B is a 37-item self-report questionnaire that evaluates several QoL domains: physical, social/family, emotional, and functional well being. In addition, a 10-item breast cancer subscale (BCS) is specific to the experiences of women living with breast cancer and the symptoms and side-effects of treatment and includes items on anxiety, pain and body image. Participants complete the questionnaire in terms of the past 7 days and each item is scored on a 5-point scale that varies from 0 (not at all) to 4 (very much). Negatively phrased questions are reversed prior to analysis and scores are summed for each domain and a higher score indicates higher well being [20]. Domain scores vary from 0 to 28 for the physical, social/family and functional well being domains; 0 to 24 for the emotional well being domain; and 0 to 40 for the BCS. The scores of the four well-being domains are summed to calculate the Functional Assessment of Cancer Therapy-General (FACT-G) score and total scores of the FACT-G and BCS are summed to calculate a FACT-B score.

##### 3.7.2.2 Fatigue

The Functional Assessment of Chronic Illness Therapy-Fatigue Scale (FACIT-Fatigue) is used to assess specific functional and physical aspects of fatigue associated with breast cancer diagnosis and treatment. This 13-item subscale has been determined to be a reliable and valid stand alone measure of fatigue [21]. In common with the FACT-B, items are scored on a 5-point likert scale and relate to the past 7 days. FACIT-Fatigue scores vary from 0 to 52 and negatively worded items are reversed before analysis so that higher scores represent better self-reported health [20].

##### 3.7.2.3 Employment status

A non-validated questionnaire will measure change in employment status in terms of five indicators: earnings, job, role, hours worked, or employment type (i.e., part-/full-time employment).

##### 3.7.2.4 Socio-demographic and clinical information

A structured questionnaire is used to collect data on date of birth, postcode, total household income, clinical diagnosis, and other conditions for which participants are currently receiving treatment. Consent will also be sought to access participants' hospital clinical notes to accurately identify diagnosis and treatments administered.

### 3.8 Data analysis

The study will provide data on eligibility, recruitment rates and possible loss to follow-up informing the feasibility and development of a larger, more definitive, future trial. The study will also assess the possibility of stratifying the sample in a larger trial by potential study confounders such as age, sex, employment type, hours of work, socio-economic status, co-morbidity and cancer stage that have previously been identified as impacting on length of absence from work [11].

As this is a feasibility study, hypothesis testing must proceed cautiously. However, it is anticipated that participants referred to VR services will experience fewer days off work due to sickness, lower levels of fatigue and increased QoL. QoL measures will be analysed at global (i.e., summed FACT-G and FACT-B scores), sub-scale (i.e., physical, social/family, emotional, functional, BCS), and individual question level. This will also enable evaluation of the outcome questionnaire's ability to detect differences in QoL between the intervention and control group associated with VR intervention. The greatest difference may be detectable at the level of individual domains of well-being (particularly, emotional, social/family and functional) and individual questions included in these domains (e.g., "I am satisfied with how I am coping with my illness" [GE2], "I feel close to my friends" [GS1], "I get support from my friends" [GS3], "I am able to work (include work at home)" [GF1], "My work (include work at home) is fulfilling" [GF2]) as support to remain in or return to employment may increase emotional well-being, enable access to a wider network of social support through colleagues, and increase physical functioning.

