### 2.1 Objectives

1. Determine the numbers of patients in Lothian and Tayside with breast cancer referred for surgery who are in paid or self-employment and potentially eligible for the RCT.

2. Assess whether it is feasible and acceptable to recruit patients into the trial post-operatively. If not, identify the most appropriate timing for recruitment and the employment intervention that follows.

3. Estimate trial recruitment rates (i.e., percentage of eligible women who consent to the trial) and attrition over the period of the trial.

4. Determine whether the outcomes are measurable and appropriate, and evaluate the instruments used to measure secondary outcomes (i.e., FACT-B, FACIT-Fatigue).

5. Estimate the likely effect size to inform the power calculation for a larger, more definitive trial.

6. Assess the feasibility of including patients with lung and prostate cancer in a larger future RCT.

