#### 3.8.1 Statistics

Data analysis will be conducted using PASW Statistics (Version 17) [22]. Baseline characteristics will be reported as mean and standard deviation for continuous data and n (%) for categorical data. Differences between the intervention and control groups for the primary outcome measure will be tested using an independent samples t-test. Differences between groups in secondary outcome measures will be examined by analysis of covariance adjusting for baseline values. Significance level is set at 0.05.

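### Section 3.8 offers the between-arm QoL comparison as evidence of how well the questionnaire detects differences, but that contrast cannot separate an unresponsive instrument from an absent or small VR effect

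*Protocol article*

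**What the plan says.** Objective 4 (section 2.1) asks whether the outcomes are measurable and appropriate, and undertakes to "evaluate the instruments used to measure secondary outcomes (i.e., FACT-B, FACIT-Fatigue". Objective 5 is a separate aim: "Estimate the likely effect size to inform the power calculation for a larger, more definitive trial".

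Section 3.8 sets out the levels of analysis: "QoL measures will be analysed at global (i.e., summed FACT-G and FACT-B scores), sub-scale" and individual question. It then draws a conclusion about the instrument: "This will also enable evaluation of the outcome questionnaire's ability to detect differences in QoL between the intervention and control group associated with VR intervention". After that it suggests which domains and items may show the largest difference.

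Section 3.8.1 gives the method: "Differences between groups in secondary outcome measures will be examined by analysis of covariance adjusting for baseline values". It adds: "Significance level is set at 0.05".

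The benefit of VR is an expectation only: "it is anticipated that participants referred to VR services will experience fewer days off work due to sickness, lower levels of fatigue and increased QoL". The same paragraph of section 3.8 advises caution over hypothesis testing.

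**The concern.** The null hypothesis of the between-arm ANCOVA is that referral to VR leaves mean QoL unchanged. It is not that the questionnaire fails to register real change. The observed contrast reflects two unknowns together: how far VR shifts QoL, and how well the score picks up a shift. The first is something the pilot exists to learn, so it cannot be taken as known in order to infer the second. The problem is one of identification and would remain with one pre-chosen score.

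What is at stake is the choice of outcome measure for the larger trial. A flat comparison could be taken as a weakness of FACT-B when VR has little effect on QoL or the pilot is too small. In the other direction, a few significant items among many could be taken as the sensitive ones when they arose by chance.

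**Working it through.** **The plan's own figures.** Section 3.2.2 gives an SD of 100 days, a 5% level and 80% power. The formula is n per arm = 2(1.960 + 0.842)² × (SD/difference)².

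| Difference | n per arm | Stated |
|---|---|---|
| 70 days | 32.04, so 33 | 35 |
| 60 days | 43.6, so 44 | 44 |
| 30 days | 174.4, so 175 | 175 |

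The figures reproduce with a two-sided test; 35 per arm for 70 days is slightly conservative. They concern days absent. No figure is given for QoL.

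**Inputs for the QoL contrast.** From the article: 35 per arm, 1:1 allocation, ANCOVA on baseline, level 0.05 (taken as two-sided). Not in the article, so assumed: true VR effect δ from 0 to 0.7 SD, and baseline-to-follow-up correlation ρ from 0 to 0.7.

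**Chance of a non-significant arm contrast.** The noncentrality is λ = δ / √[(1 − ρ²) × 2/35], referred to a noncentral t. For δ = 0.3 and ρ = 0.5, λ = 0.3 / √(0.75 × 0.0571) = 1.45.

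| True VR effect (SD) | ρ = 0 | ρ = 0.5 | ρ = 0.7 |
|---|---|---|---|
| 0 | 95% | 95% | 95% |
| 0.25 | 82% | 78% | 70% |
| 0.3 | 76% | 70% | 59% |
| 0.5 | 46% | 34% | 18% |
| 0.7 | 18% | 8.5% | 2% |

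If being back at work also shifts QoL by 0.8 SD in half the women, that variation adds 0.8² × 0.25 = 0.16 to the residual variance (0.75 becomes 0.91). At ρ = 0.5 the miss rate at 0.25 SD is then about 81-82%, and at 0.5 SD about 42-43%. Hence the range of 70-82% for effects of 0.25 to 0.3 SD.

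The smallest effect detectable with 80% power is 2.802 × √(2/35) = 0.67 SD, or 0.67 × √0.75 = 0.58 SD at ρ = 0.5.

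**Does the contrast tell a good instrument from a poor one?** Let reliability R shrink the observed effect to δ√R, with ρ = 0.
- δ = 0: 95% non-significant at R = 1.0 and at R = 0.5.
- δ = 0.3 SD: 76% at R = 1.0 and 86% at R = 0.5.

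With no VR effect the result carries no information on the instrument. With a modest effect it carries little.

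**The converse error.** Two global scores, five subscales and 37 items make 44 comparisons per time point. With no VR effect, 44 × 0.05 = 2.2 are expected to be significant. The chance of at least one is 1 − 0.95⁴⁴ = 90% if they were independent. Items are correlated, so that figure is at the upper end.

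**An alternative that does not need VR to work.** Both arms are pooled, with 70 women, and women at work are compared with those off sick at ρ = 0.5. The standard error is √[0.75 × (1/n₁ + 1/n₂)]: 0.207 with 35 and 35, and 0.345 with 7 and 63. All effects here are assumed.

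| Association with work status (SD) | Half back at work | 10% back at work |
|---|---|---|
| 0.8 | about 96% power | about 60-63% |
| 0.5 | about 64-66% | about 30% |
| 0.3 | about 30% | about 14% |

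**The case against.** The strongest reply is that the article states no decision rule. A reader might infer that FACT-B fails if the arms do not differ at 0.05, or that it would then be dropped. The text supports neither: section 3.8 says only that the analysis makes an evaluation possible, the 0.05 level in section 3.8.1 is not tied to it, and caution is advised. A reader might also infer that a sound instrument looks insensitive every time VR has no effect. That is too strong, since 5% of single tests would still be significant and some of 44 comparisons probably would be.

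It can also be said that section 3.8 asks which score level shows VR-related differences best. That is a fair exploratory question for a pilot and should be kept. Even so, its answer depends on VR having an effect.

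Leaving detail to a fuller protocol or analysis plan would be acceptable. The point here, however, is an inference that the article states. Reading estimates instead of p-values does not remove the confounding. Nothing else shown fills the gap: the service-recorded scales (section 3.5) cover the intervention arm and are not linked to FACT-B, and the interview topics in section 3.9.1 do not mention the questionnaires.

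The reply has most force against the alternative. A null result against work status is also ambiguous, because being at work may not change QoL. Items GF1 and GF2 ask about work, so the anchor is partly circular. Section 3.2.2 assumes a control mean of 180 days absent in six months, which fits poorly with half the women being back at work. The 96% figure should not be taken as typical.

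**Conclusion.** The concern holds as a flaw in a stated inference, of moderate weight. The between-arm contrast is the only quantitative evidence on responsiveness that the article offers for Objective 4, and it cannot distinguish an unresponsive questionnaire from an ineffective or weakly effective intervention. The 95% figure under no VR effect follows from the 0.05 level alone and does not depend on sample size or instrument quality. The 70-82% for effects of 0.25 to 0.3 SD rests on 35 women per arm and an assumed baseline correlation of 0.5, since the article gives no QoL effect size, SD or correlation.

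The point does not touch randomisation, data collection, the primary analysis or the validity of the ANCOVA as an estimate of the VR effect. Nor do the documents support a claim that an analysis by work status would reliably vindicate a sound instrument.

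**What to change.** 1. In section 3.8, keep the exploratory comparison by score level, reported as an estimate of the VR effect with 95% confidence intervals. Add that the absence of an arm difference, or its isolated presence, will not be read as evidence about the instrument.
2. For Objective 4, add a descriptive responsiveness analysis pooled over arms and adjusted for arm. Relate change from baseline to 6 months in FACT-B (total and subscales) and FACIT-Fatigue to work status or days absent in the last four-weekly report before month 6. Report differences and standardised response means with 95% confidence intervals.
3. Repeat the FACT-B part without items GF1 and GF2.

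The cost is a few sentences and some extra analyses. Section 3.6 already provides the questionnaires and the four-weekly absence reports in both arms, so no new patients, forms or visits are needed. The downside is that work status is an imperfect anchor. Precision depends on how many women are back at work and on the size of the association: power runs from about 30% to 96% under the assumed inputs, and lower if both are weak. The result would describe responsiveness, not prove it.

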#### 3.8.1 Statistics

Data analysis will be conducted using PASW Statistics (Version 17) [22]. Baseline characteristics will be reported as mean and standard deviation for continuous data and n (%) for categorical data. Differences between the intervention and control groups for the primary outcome measure will be tested using an independent samples t-test. Differences between groups in secondary outcome measures will be examined by analysis of covariance adjusting for baseline values. Significance level is set at 0.05.

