#### 3.2.2 Sample size calculation

There are several uncertainties that this feasibility study seeks to address before a larger, more definitive RCT of vocational rehabilitation services for people with cancer can be conducted. These uncertainties include: (1) the number of women who may be eligible for inclusion in the trial; (2) the percentage of eligible women who meet the VR services' criteria for referral; (3) the recruitment rate, defined as the percentage of eligible women who consent to involvement in the trial. The feasibility study will therefore provide evidence to inform sample size calculations for a larger trial. However, we estimate that between 66 and 79 patients will be recruited to the feasibility study over a 6 month period. This sample size is based on diagnosis and surgical data obtained from 2008, estimated employment rates, and a conservative recruitment rate of between 50% and 60%.

The feasibility study is also assessing the likely effect size to inform sample size calculations for a potential larger future trial. The primary outcome measure is the number of days off work in the 6 months following surgery. One report indicated that the mean length of time absent from work after a diagnosis of breast cancer was 5.6 months [12]. Assuming, therefore, a mean of 180 days absent from work in the control group and an estimated standard deviation of 100 days, with a sample size of 70 (35 in each group), the study would be able to detect a reduction in number of days absent from work from 180 to 110 days with 5% level of significance and 80% power. A larger sample size would be required to detect smaller differences. To detect a reduction in number of days absence by 2 months, a sample size of 88 patients (44 in each group) would be required. To detect a reduction of 1 month, a sample size of 350 (175 in each group) would be required.

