### 3.4 Randomisation

The allocation sequence was generated from a Bernoulli probability distribution with a specified probability of 0.5 which ensures participants have an equal chance of being in either group. Participants are randomly assigned to the intervention and usual care arm with a 1:1 allocation ratio (Figure 1). A separate sequence is used for each NHS Board (analogous to the VR service to which participants in the intervention arm are referred) to ensure that there is an even distribution of participants to the intervention and usual care groups in each NHS Board. The allocation sequences are concealed from the researchers responsible for recruiting patients into the trial (RGK), data collection (RGK) and data analysis (RGK, JE, NMG, GH). The trial statistician (DA) provided the allocation sequences to an administrator in the Cancer Care Research Centre at the University of Stirling who is not involved in the process of random number generation nor data collection and analysis. This individual will assign patients to the intervention and usual care groups and refer patients in the intervention arm to the VR service.

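### The primary analysis is an unadjusted t-test; adding NHS Board and one or two collected baseline factors would sharpen the effect estimate at almost no cost

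*Protocol article*

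**What the plan says.** - **Primary analysis (Section 3.8.1):** "Differences between the intervention and control groups for the primary outcome measure will be tested using an independent samples t-test". No covariate is mentioned.
- **Secondary analyses (Section 3.8.1):** "Differences between groups in secondary outcome measures will be examined by analysis of covariance adjusting for baseline values". The adjustment is for the baseline value only; Board is not included.
- **Randomisation (Section 3.4):** sequences come from a Bernoulli distribution with probability 0.5, and no blocking is described. "A separate sequence is used for each NHS Board", with the stated purpose of balancing the arms within each Board. Board also determines the VR service (Section 3.5).
- **Prognostic factors (Section 3.8):** age, sex, employment type, hours of work, socio-economic status, co-morbidity and cancer stage are listed as factors "that have previously been identified as impacting on length of absence from work". The article considers them only as possible stratifiers for a larger trial.
- **Data collected:** hours worked and employment type (Section 3.7.2.3, collected at baseline according to Section 3.6); date of birth, postcode, household income, diagnosis and other treated conditions (Section 3.7.2.4).
- **Purpose:** objective 5 in Section 2.1 is to estimate the effect size for the definitive trial's power calculation.

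**The concern.** Length of absence is the primary outcome, and the article itself says which patient characteristics drive it. Several are recorded on every participant, and Board is known for all of them. Leaving them out of the primary model puts the variation they explain into the error term. Any chance imbalance in them also goes into the estimated difference.

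Such imbalance is likely here. A Bernoulli sequence within each Board does not hold the arms level, so the separate sequences do not deliver the balance that Section 3.4 intends, and the analysis does not compensate. What is at stake is the width of the interval around the effect estimate that goes into planning the definitive trial. The unadjusted analysis also yields no residual SD, which that trial would need if it adjusts or stratifies.

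**Working it through.** **1. The plan's own figure.** Inputs from Section 3.2.2: power to "detect a reduction in number of days absent from work from 180 to 110 days", "an estimated standard deviation of 100 days", "with 5% level of significance and 80% power", 35 per group. Sidedness is not stated; two-sided fits.

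n per group = 2 × (1.960 + 0.842)² × 100² / 70² = 32.0, so 33 (34 with the t distribution), against 35 stated. For 60 days the formula gives 44, and for 30 days 175, both as stated. One-sided testing would give 26, 35 and 138, which does not fit. The sizes are therefore those of an unadjusted two-sided comparison.

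**2. Precision of the planned t-test at 35 per arm.** SE = 100 × √(2/35) = 23.9 days; 95% CI half-width 47.7 days; power for 70 days 82.3%; difference detectable with 80% power 67.9 days.

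**3. Precision after adjustment.** With k covariate terms, N = 70 and proportion of variance explained R² (assumed):

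variance ratio = (1 − R²) × (N − 3)/(N − k − 3), with N − 2 − k degrees of freedom.

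The second factor charges for chance imbalance in the covariates. For k = 3 (Board plus two factors) it is 67/64 = 1.047. Equivalent size is 35 divided by the variance ratio.

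| R² (assumed) | Variance ratio | Equivalent n per arm | CI half-width (days) | Power for 70 days | Detectable difference (days) |
|---|---|---|---|---|---|
| t-test | 1.000 | 35 | 47.7 | 82.3% | 67.9 |
| 0 | 1.047 | 33.4 | 48.8 | 80.5% | 69.6 |
| 0.1 | 0.942 | 37.2 | 46.3 | 84.4% | 66.0 |
| 0.2 | 0.838 | 41.8 | 43.7 | 88.3% | 62.2 |
| 0.3 | 0.733 | 47.7 | 40.9 | 92.1% | 58.2 |

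The variance ratio and equivalent size do not depend on the SD; the other columns take the plan's 100 days as given.

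**4. Break-even.** Adjustment pays once R² exceeds 1 − (N − k − 3)/(N − 3): 1 − 66/67 = 0.015 for one term, 1 − 64/67 = 0.045 for three, 1 − 60/67 = 0.104 for seven. A short model is safe. The full list is less clearly so, and sex is constant because all participants are women.

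**5. Board alone, simulated.** Two Boards of 35 (an assumption), Bernoulli allocation within each, total SD 100, normal outcomes, 6,000 runs per setting:

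| Board difference (assumed, days) | R² | Power for 70 days, t-test | Power, Board-adjusted |
|---|---|---|---|
| 0 | 0 | 82.0% | 81.5% |
| 40 | 0.04 | 81.2% | 82.0% |
| 60 | 0.09 | 81.7% | 84.8% |
| 100 | 0.25 | 81.0% | 90.0% |

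Type I error stayed between about 4.5% and 5.5% for both analyses.

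**6. How often Board is unbalanced.** With 35 patients per Board, the arms differ in Board share by 10 percentage points or more in about 40% of trials and by 20 or more in about 11%.

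**The case against.** The strongest reply is that nothing here is invalid. Two independent Bernoulli sequences with probability 0.5 are statistically the same as one simple sequence, so no restriction has to be carried into the analysis. That stands, and the simulation agrees. A reader might infer that ignoring the randomisation factor distorts the test; under unblocked allocation it does not.

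Four other stronger readings also lack support in the article:

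- **Inconsistency with the secondary outcomes.** The secondary ANCOVAs adjust for the same measure at baseline. Days off work after surgery has no such baseline, so the contrast is no contradiction.
- **Board as a proxy for hospital and recruitment route.** Board sets the VR service, but Tayside has two hospitals with different consent routes (Sections 3.3.1 and 3.3.2). A Board term does not capture those. Nor does a Board main effect address a different treatment effect by service.
- **The unadjusted SD as the wrong planning input.** Section 3.8 only considers whether a later trial might stratify. The unadjusted SD matches Section 3.2.2 and is conservative if the later trial adjusts.
- **A gain to 39–50 per arm.** This comes from 35/(1 − R²) with R² of 0.1 to 0.3 and ignores the cost of estimating the covariates.

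It is also fair that this is a feasibility study in which the article says testing must be cautious, that stage is not a named data item, and that no R² or Board difference is given. Imbalance in any one trial may be minor. If a 20-patient Board split 13:7, a 50-patient Board split 25:25 and Boards differed by 40 days, the shift would be (13/38 − 7/32) × 40 = 4.9 days, about a fifth of the 23.9-day SE. Caution about testing does not, however, argue against a tighter estimate. The primary test is also stated outright rather than left to an analysis plan.

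**Conclusion.** The point holds as a precision improvement. The planned t-test is valid but gives up information that the article identifies as relevant to the outcome and largely collects. Under an assumed R² of 0.1 to 0.3 for Board plus two factors, adjustment is worth about 2 to 13 extra patients per arm (37 to 48 against 35) and about 2 to 10 points of power for a 70-day difference. If the factors explain nothing, the cost is about 0.5 points for Board alone and 1.8 points (82.3% to 80.5%) for three terms.

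The size depends on the assumed R², on equal arms of 35 and on the plan's SD of 100 days. The direction needs only an R² above about 0.045 for three terms, a low threshold for factors described as affecting absence.

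**What to change.** In Section 3.8.1:

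- Make the primary analysis a linear model of days absent on arm, NHS Board and one or two prespecified baseline factors already collected, for example age and baseline hours worked. Use cancer stage only if it can be obtained reliably from the hospital notes.
- Report the adjusted mean difference with its 95% CI.
- Report both the unadjusted and the residual SD, so that the definitive trial can be planned either way.
- Keep the independent samples t-test as a sensitivity analysis.
- Add Board to the secondary ANCOVAs.

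The cost is a few sentences of protocol text and a few lines of analysis code. The sample size in Section 3.2.2 can stay as it is, and Board, age and hours need no new data collection. The covariates should be fixed before outcome data are examined by arm, so that the choice cannot follow the result.

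### Baseline-adjusted ANCOVA at 0.05 is set for all secondary outcomes: it does not fit the categorical employment indicators, and applied to single QoL questions it is weak evidence about the questionnaire

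*Protocol article*

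**What the plan says.** Section 3.7.2 of the protocol article names the secondary outcomes: "Secondary outcome measures are changes in quality of life (QoL), fatigue and employment status". Section 3.7.2.3 defines the last of these as "change in employment status in terms of five indicators: earnings, job, role, hours worked, or employment type", with employment type explained as part-time or full-time, all collected by a non-validated questionnaire.

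Section 3.8.1 assigns a single method to the whole group: "Differences between groups in secondary outcome measures will be examined by analysis of covariance adjusting for baseline values". It makes no exception for any outcome, and adds: "Significance level is set at 0.05".

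Section 3.8 sets the depth of the quality-of-life (QoL) analysis: "QoL measures will be analysed at global (i.e., summed FACT-G and FACT-B scores), sub-scale (i.e., physical, social/family, emotional, functional, BCS), and individual question level". It then says that working at these levels will help to evaluate whether the questionnaire can pick up differences between the arms linked to vocational rehabilitation (VR). Objective 4 in section 2.1 makes evaluation of FACT-B and FACIT-Fatigue one of the study's purposes. Section 3.8 also asks for caution in hypothesis testing because this is a feasibility study, but it attaches no rule to that caution.

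**The concern.** There are two separate difficulties.

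The first is a mismatch between method and outcome. ANCOVA compares means of a numeric outcome after adjusting for the same quantity at baseline. Job and role are nominal: there is no mean to compare and no numeric baseline to put in the model. If an indicator is recorded only as changed or unchanged since baseline, the change is itself the outcome and has no baseline value. An analyst following section 3.8.1 literally could not analyse these indicators, although employment status is the secondary outcome closest to the aim of the intervention.

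The second is the use made of many comparisons at an unadjusted 0.05. A questionnaire with 37 questions, tested question by question at two follow-ups, is expected to show some significant differences even if VR referral does nothing. If those differences are read as showing where the instrument is sensitive, chance results in roughly 70 women become evidence about measurement in the larger trial.

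**Working it through.** **1. Method against indicator.** Setting section 3.8.1 beside the five indicators in section 3.7.2.3:

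| Indicator | Nature | Baseline-adjusted ANCOVA? |
|---|---|---|
| Job | nominal, or changed/unchanged | no |
| Role | nominal, or changed/unchanged | no |
| Employment type (part-/full-time) | binary, with a baseline value | workable as a linear model for a risk difference |
| Hours worked | numeric if recorded as hours | yes, if so recorded |
| Earnings | numeric if recorded as an amount | yes, if so recorded |

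Any of the last three moves to *no* if the form records only whether it changed. The article does not say how the indicators are coded, so job and role are the certain mismatches and the others depend on the form.

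**2. Number of tests.** The item count can be checked against the domain ranges in section 3.7.2.1. Each item scores at most 4, so:

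- physical, social/family and functional domains: 28/4 = 7 items each
- emotional domain: 24/4 = 6 items
- breast cancer subscale: 40/4 = 10 items
- total: 7 + 7 + 7 + 6 + 10 = 37, which agrees with the stated 37.

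Measures at each follow-up: 37 items + 5 sub-scales + 2 totals (FACT-G, FACT-B) + 1 fatigue score = 45. The employment indicators and the single fatigue items are not counted. Section 3.6 gives two follow-ups for these outcomes, 6 and 12 months: 45 × 2 = 90 tests.

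**3. Expected false positives with no effect.** Expected number = tests × 0.05.

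- One follow-up: 45 × 0.05 = 2.25
- Both follow-ups: 90 × 0.05 = 4.5

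Correlation between the tests does not alter this expectation; it makes the count more variable.

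**4. Chance of at least one false positive among 90.**

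- Independent tests: 1 − 0.95^90 = 0.99.
- Test statistics with a common correlation ρ, two-sided at 0.05: 1 − ∫ [Φ((1.96 − √ρ z)/√(1−ρ)) − Φ((−1.96 − √ρ z)/√(1−ρ))]^90 φ(z) dz. This gives 0.93 at ρ = 0.3 and 0.75 at ρ = 0.5.

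The article gives no correlations, so 0.3 and 0.5 are assumptions.

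**5. Check by simulation.** ANCOVA was run on null data for the 44 QoL measures (fatigue left out): five-level items, 35 women per arm, and assumed correlations of 0 to 0.6 within domains, 0 to 0.4 between domains and 0.5 to 0.6 between time points.

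| | 6 months | 6 and 12 months |
|---|---|---|
| Mean number of false positives | 2.0 to 2.2 | about 4.4 |
| Chance of at least one | 0.67 to 0.88 | 0.89 to 0.98 |
| Chance of at least three | 0.24 to 0.37 | 0.52 to 0.78 |

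The means agree with 44 × 0.05 = 2.2 and 88 × 0.05 = 4.4.

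**The case against.** Several points on the other side are sound and limit the finding.

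- **A reader might infer that employment status is left with no valid comparison at all.** The article does not support that. Hours and earnings suit ANCOVA if recorded as amounts. Part-/full-time type is binary with a baseline value, and a baseline-adjusted linear model on a 0/1 outcome estimates a risk difference. In a null simulation with 35 per arm and an assumed 40% at baseline, such a model rejected 4.9% of the time.
- **A reader might add that all women are employed at entry, so being in work has no baseline variation.** True, but being in or out of work is not one of the five indicators in section 3.7.2.3.
- **A reader might object to ANCOVA on items scored 0 to 4.** The simulation used five-level items and the rejection rate stayed close to nominal, so the scale does not inflate error.
- **A reader might infer that outcomes for the definitive trial will be picked by p-value.** No section says so. Section 3.8 speaks only of evaluating the questionnaire, and names beforehand the domains and example questions thought most likely to differ.
- **The count of 90 joins two sections.** Section 3.8 says QoL is analysed at question level, and section 3.8.1 supplies the method and the level. Applying one to the other is a fair reading but is not spelled out.
- **Multiplicity rules and a model for each indicator are often left to a full protocol or SAP, and the article asks for caution.** Their absence from an article would not be a fault.

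What survives is what the article does fix: one method and one significance level for all secondary outcomes. A fuller plan that followed it would carry the mismatch for job and role. The call for caution limits neither which tests are done nor how they are read, and the named questions are given only as examples.

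**Conclusion.** The point holds in two limited parts. First, section 3.8.1 prescribes a method that cannot be used for job and role, nor for any employment indicator recorded only as changed or unchanged. How far beyond job and role this reaches depends on coding that the article does not describe.

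Second, if the same rule is applied at the question level of section 3.8, 90 tests carry about 4.5 expected false positives when there is no effect. Significant single items would then be weak evidence of the questionnaire's ability to detect a VR effect. The figure of 4.5 rests on the count of measures and on every one being tested at 0.05 at both follow-ups. The chance of at least one, 0.75 to 0.99, also rests on the assumed correlations. These are expectations under no effect, not a forecast that several false positives must occur.

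The matter is worth correcting but secondary. It does not touch the primary outcome, the sample size, or the recruitment and attrition estimates.

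**What to change.** Reword sections 3.8 and 3.8.1 as follows.

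- **Employment status.** Compare change in job, change in role and other categorical indicators as proportions by arm, using a risk difference with 95% CI or logistic regression. Keep ANCOVA for hours and earnings where these are recorded as numbers.
- **Tested scores.** Name the FACT-B total and FACIT-Fatigue as the secondary scores to be tested, by ANCOVA adjusted for baseline. At two follow-ups this is 4 tests: 4 × 0.05 = 0.2 expected false positives, and a chance of at least one of 1 − 0.95^4 = 0.19 if independent.
- **Sub-scales and items.** Report sub-scales as adjusted differences with 95% CIs. Report single questions descriptively, without significance tests.
- **Evaluation of the instruments.** Judge them on completeness, floor and ceiling effects, and estimates with CIs, not on which items reach p < 0.05.

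The cost is a few sentences and less analysis than now planned. The one loss is the item-level p-values.
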